### Randomization and Blinding

Employees accumulating fewer than 10,000 steps per day during the baseline period (study weeks 1 and 2) will be randomized using a single, constant allocation ratio (1:1) to standard care or intervention groups. Randomization will occur using an online random number generator [40]. Participants will not be blinded to study group allocation. The research analysts will be blinded to group allocation until after the study is completed.

### Statistical Analyses

For each participant on each day of the study (participant-day level) continuous step count data will be obtained and screened for outliers (less than 100 steps per day, more than 50,000 steps per day) [31]. If participants did not synchronize their accelerometer for at least 3 separate workdays at T2 and T3, the last observation will be carried forward using T1 or T2 means [33]. This procedure conservatively assumes no change in variables and allows analysis by intention-to-treat. The step count data will then be dichotomized at the participant-day level to create a binary variable where participants achieved (value = 1) or did not achieve (value = 0) their step goal. Using this binary variable, the mean proportion of participant-days where step goals were achieved at week 24 will be compared.

SPSS version 21.0 (IBM Corp) will be used to fit a generalized linear model with participant random effects, a random intercept, time-fixed effects (T1-T3), and treatment-fixed effects (by study group). A binomial distribution with logit link for models using the binary outcome will be used to estimate the adjusted difference in the proportion of participant-days step goal achieved, and the bootstrap procedure and resampling of participants will be used to obtain 95% confidence intervals and *P* values. Comparisons across study groups will be adjusted for mean steps per day (baseline), age, gender, and income since these have moderated incentive-effects in the past [41]. The same procedures will be used to analyze T2 (ie, intervention end) binary data.

For continuous step count (ie, mean steps per day) and bout minutes (ie, total minutes of MVPA in 10-minute bouts per week) data at T2 and T3, a generalized linear model will be used, as above, except the difference in steps per day and MVPA bout minutes between groups will be obtained using least-squares means. Also, a repeated measures analysis of variance using linear mixed models with first order autoregressive covariance structures will be used to compare changes in self-determined motivation and self-efficacy between groups. Adherence will be analyzed using *t* tests comparing the mean number of missing step count entries per week and mean number of website log-ins per month between groups. This protocol is registered with ClinicalTrials.gov [NCT02638675].

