### Standard Care Group

Standard care group participants will have access to Change4Life and will receive the standard minimal chance-based incentives (ie, less than 1 in 100 chance of earning Can $5 to $20 [US $3.70-$14.80] vouchers) for completing learning modules and health tasks. In addition, standard care participants will be asked to wear the accelerometer, which tracks steps and 10-minute bouts of MVPA per day, synchronize the device to the Change4Life program daily, and reach tailored daily step count goals for 10 weeks (weeks 3 to 12). Standard care participants will be instructed to increase their daily step counts by 1000 steps above their baseline average every 2 weeks until they reach the target goal of 3000 extra steps at week 7 (see Table 1). Change4Life will automatically calculate the average baseline value in the early hours of day 1, week 3 using data uploaded the previous 2 weeks (the Run-In period)—days with step counts less than 100 or greater than 50,000 will not be included in calculations [31]. This tailored and graded approach to setting step goals is more realistic than the traditional 10,000 step target (ie, the average Canadian adults accumulates only about 5000 steps per day) [32], may increase chances of intervention success (versus offering a lofty 10,000 step per day goal for everyone), and has worked well in employee populations in the past [33].

**Table 1 table1:** Daily step count goals across the Change4Life program.

Study week	Step count goal
Weeks 1-2	2-Week Run-In (to confirm lower active status and calculate daily step count average)
Weeks 3-4	Increase daily steps by 1000 above baseline average
Weeks 5-6	Increase daily steps by 2000 above baseline average
Weeks 7-8	Increase daily steps by 3000 above baseline average
Weeks 9-12	Maintain steps at 3000 above baseline average

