### Intervention Group

The only difference between the standard care and intervention groups will be the addition of the guaranteed incentive (Can $1 [US $0.74] per day). During the intervention period (weeks 3 to 12), intervention group participants will be eligible to earn Can $1 (US $0.74) in vouchers (eg, groceries, coffee, or movies) each time tailored daily step goals are achieved. The total amount available over the intervention period will be Can $70 (US $51.82). Previous research suggests that as little as Can $6.75 (US $5) per week may be sufficient to produce favorable lifestyle health behavior changes [34], thus Can $7 (US $5.18) per week (Can $1 [US $0.74] per day) was chosen as the size of the incentive. During the study follow-up period (weeks 13 to 24), intervention participants will no longer receive the per day reward for reaching daily step goals.

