### Outcome Measures

The primary study outcome will be the mean proportion of participant-days that step goals are achieved during week 24 (the postintervention follow-up assessment period, T3). Mean proportion of participant-days that step goals are achieved during week 12 (intervention end point, T2) and volume of steps and 10-minute bouts of MVPA per week at T2 and T3 will be secondary outcomes. Physical activity will be objectively assessed using the StepsCount Piezo Rx accelerometer (StepsCount Inc, Deep River, ON, Canada). The Piezo Rx is a medical-grade device with a single axis piezoelectric sensor. This device has been found to be valid in calculating step counts and MVPA among adult participants [35,36]. Standard care and intervention participants will be encouraged to wear their accelerometer and synchronize it to the Change4Life program during the baseline 2-Week Run-In period (T1), as well as at the intervention end point (T2), and follow-up assessment (T3) with Can $10 (US $7.40) study retention vouchers; these vouchers for assessment completion will help minimize dropout and will not be contingent on step goal achievement.

The adherence outcome variables will be mean number of missing step count entries per week as well as mean number of Change4Life website log-ins in general. Participants’ self-determined motivation to exercise will be examined using the Behavioral Regulation to Exercise Questionnaire-3 (BREQ-3) [37,38]. Participants’ walking self-efficacy will be assessed using a modified version of the Self-Efficacy for Exercise Scale (SEE Scale) [39]. The BREQ-3 and the SEE Scale will be administered online at baseline (T1), intervention end point (T2), and during the follow-up assessment period (T3). The differential impact of the Can $1 (US $0.74) per day incentive on the various physical activity outcomes will be explored. For instance, we may find that while the guaranteed incentives stimulate step goal achievement at T2, they also undermine self-determined motivation and thus the prospect that people will continue to exercise after the incentive is removed.

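### The 3-workday minimum does not match an all-days outcome and, on its natural reading, replaces real week-24 observations with an earlier mean

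*Protocol article*

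**What the plan says.** In the protocol article, Statistical Analyses sets the data-sufficiency rule: "If participants did not synchronize their accelerometer for at least 3 separate workdays at T2 and T3", then "the last observation will be carried forward using T1 or T2 means". It justifies this as follows: "This procedure conservatively assumes no change in variables and allows analysis by intention-to-treat". The next step is: "The step count data will then be dichotomized at the participant-day level to create a binary variable". The term *workday* is not defined, and no sentence says what happens to days that were observed in a week that fails the rule.

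Three other sections work with all days:

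- Outcome Measures: "The primary study outcome will be the mean proportion of participant-days that step goals are achieved during week 24". There is no restriction to workdays.
- Standard Care Group: the personal goal comes from the run-in average, and the only exclusion is that "days with step counts less than 100 or greater than 50,000 will not be included in calculations".
- Intervention Group: "thus Can $7 (US $5.18) per week (Can $1 [US $0.74] per day) was chosen as the size of the incentive", which is a seven-day week.

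**The concern.** The test of whether a week has enough data uses a different kind of day from the outcome, the goal and the reward. A participant can have three, four or more valid days in week 24, fail because too few of them were workdays, and have the week represented by an older mean.

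The trial asks whether activity persists once payment stops. Putting a week-12 value in place of an observed week-24 value brings paid behaviour into the unpaid assessment, in the intervention arm only. Putting a baseline mean there scores the person as never reaching the goal. In both cases primary-endpoint data already in hand are given up. This is a consequence of an explicit rule, so it is not a detail that a condensed article has simply left to a fuller document.

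**Working it through.** **1. Do all seven days count?** The reward is Can $1 per day over weeks 3 to 12, which is 10 weeks. 10 × 7 × Can $1 = Can $70, the total stated in Intervention Group. So goals and rewards run on every day, and the outcome is defined on participant-days.

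**2. The plan's sample size.** Inputs from Sample Size are 0.40 vs 0.20, 80% power, two-sided 0.05 and, from Randomization and Blinding, 1:1 allocation. The unpooled formula gives (0.40 × 0.60 + 0.20 × 0.80) × 7.849 / 0.20² = 0.40 × 7.849 / 0.04 = 78.5, so 79 per group and 158 in all. This reproduces the stated figure. It is used here only to turn shares into head counts.

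**3. How many real days can be lost?** Let W be the number of workdays in the week, x the synchronized workdays and y the synchronized other days. The rule is triggered when x ≤ 2, whatever y is. The most observed days that can be replaced is 2 + (7 − W): 4 of 7 for W = 5, 5 of 7 for W = 4 and 6 of 7 for W = 3. If *workday* means a day actually worked, a person on leave all week can lose 7 of 7.

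**4. How often?** The documents give neither synchronization rates nor work patterns, so both are assumed. Let each day be synchronized independently with probability s. The share replaced despite 3 or more real days is P(x ≤ 2 and x + y ≥ 3).

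For W = 5 and s = 0.7:

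- x = 1, y = 2: 5 × 0.7 × 0.3⁴ × 0.7² = 0.02835 × 0.49 = 0.0139
- x = 2, y ≥ 1: 10 × 0.7² × 0.3³ × (1 − 0.3²) = 0.1323 × 0.91 = 0.1204
- Sum: 0.134, or 158 × 0.134 ≈ 21 participants

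| Workdays in week | s = 0.7 | s = 0.8 | s = 0.9 |
|---|---|---|---|
| 5 | 13.4% (about 21 of 158) | 5.3% (about 8) | 0.8% (about 1) |
| 4 | 32.0% | 17.6% | 5.2% |
| 3 | 62.8% | 48.3% | 27.1% |

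Under a minimum of any 3 of the 7 days, every entry becomes 0. The rows for 3 and 4 workdays apply only if *workday* means a day worked. Independence matters too: if missed days cluster in a few people who stop synchronizing, there are fewer partial weeks and the shares fall.

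**5. Effect on the primary contrast.** Let π be the share replaced, taken as equal in both arms and among participants otherwise like the rest. Let D12 and D24 be the true group differences in proportion at weeks 12 and 24.

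- T2 value carried: the analysed difference is (1 − π) × D24 + π × D12, so the bias is π × (D12 − D24). For each 0.10 by which the difference shrinks after payment stops, this is 0.0134 at π = 13.4%, 0.0053 at 5.3% and 0.0008 at 0.8%. The formula is approximate, because dichotomizing after carry-forward turns a mean into one all-or-nothing value.
- T1 value carried: the baseline mean is 3000 steps below the final goal in the Standard Care Group table (taken here to apply in week 24 as well), so it scores 0 in both arms. The analysed difference is (1 − π) × D24. At the planned 0.20 with π = 13.4%, that is 0.866 × 0.20 = 0.173.

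The first effect inflates the contrast whenever the group difference fades, and the second dilutes it. The direction therefore depends on which mean is carried, and the article's description of the procedure as conservative is not assured.

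**The case against.** Several points on the other side stand.

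- A minimum number of days is ordinary, and the article cites a source for its procedure. In a workplace trial there is a plausible reason not to let an assessment rest on days off alone.
- A reader might infer that all data from days off are overwritten. They are not: once 3 workdays are present, nothing in the rule removes other days. A Monday-to-Friday employee with weekend data only has at most 2 days and would fail any 3-day minimum.
- The examples of leave and long shifts depend on what *workday* means. If it is a Monday-to-Friday calendar day, a person on leave who synchronizes all week has 5 and passes.
- Overwriting is inferred. The article does not literally say that observed days are deleted, and filling only the missing days is possible, though less natural given that an assessment is set to an earlier mean on a no-change assumption.
- These weeks usually do have missing days: 2 workdays plus 2 days off leaves 3 of 7 unobserved.
- Admitting every synchronized day has a risk. Participants are unblinded and could upload only their good days, and a mixed model does not correct for that.

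The objection does not remove the mismatch. Under either meaning of *workday*, 1 or 2 synchronized workdays plus enough other days fails the rule with 3 or more real days in hand.

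**Conclusion.** The concern holds in limited form. A workday-only minimum is a poor match for an all-days primary outcome. On the natural reading it replaces real week-24 observations for participants with 1 or 2 synchronized workdays and at least 3 valid days in total. If *workday* means a day worked, it also reaches people on leave or on short shift weeks.

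With a 5-workday week and independent synchronization, the share is about 13%, 5% and 1% at 70%, 80% and 90% synchronization, and larger with fewer workdays. These are assumptions, not figures from the article. Where T2 means are carried, the bias is that share times the week-12 minus week-24 group difference, which is small if synchronization is good.

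Two stronger readings are not supported. A reader might infer a definite inflation of the type I error, but the article gives neither the share replaced, nor the expected week-12 difference, nor the participant-level variance that such a figure needs. A reader might also infer heavy summer-leave losses, because 24 weeks from the end of February 2017 is about mid-August. February is when enrollment is completed, so only the last enrollees would be assessed then. The change is worth making because it is cheap and protects the primary endpoint.

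**What to change.** Amend Statistical Analyses in three respects:

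1. Count any synchronized day with 100 to 50,000 steps, workday or not, toward the 3-day minimum.
2. State that observed T2 and T3 days are never replaced and enter the planned day-level model with participant random effects.
3. Report a sensitivity analysis limited to participants with at least 3 valid days at the assessment.

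If the workday restriction is kept for a reason, define *workday* and say what happens to observed days in a week that fails.

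The cost is a sentence or two and one extra model run, with no new data. The downside is small: some participants will contribute only a few days, possibly selectively synchronized. The random-effects model gives short records less weight but cannot remove selection, which is why the sensitivity analysis is needed as a check.

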Of the randomized controlled trials (RCTs) that have recently examined this issue [22-26], 4 have observed a regression to baseline behaviors after incentive removal [22-24,26] and only 1 has demonstrated persisting physical activity [25]. One reason for this may have to do with the limited application of health behavior change theories in the design of incentive programs [19]. It is increasingly suggested that for incentives to both stimulate and sustain health behavior change they should be grounded in theory [19,27,28]. In the single “positive” study, behavioral maintenance (ie, 16-week follow-up) was driven entirely by the lower active subgroup (ie, university students visiting the gym fewer than once per week at baseline)—possibly because exposure to the new behavior (ie, gym attendance) led to increased confidence to perform that behavior [25]. This presumption aligns well with self-determination theory, a global theory of motivation focused on the extent to which behaviors are done volitionally, which suggests that incentive programs designed to increase a person’s confidence are more likely to foster self-determined (or intrinsic) motivation [29,30]—a key driver of sustained physical activity [30].

Realizing the potential of incentives to promote sustained physical activity, therefore, will be contingent on research that improves the understanding of theoretical (eg, self-determined motivation) and contextual (eg, target group characteristics) factors that may influence incentive program effectiveness. The purpose of this protocol is to outline the design of an RCT that will examine the longer term effects of an existing physical activity promotion program that is enhanced by guaranteed incentives for lower active employees only in a real-world, ecological setting. We hypothesize that targeting lower active employees with incentives for tailored daily step goals (in addition to the generic, one-size-fits-all approach to goal setting that is typically used) may be more likely to create mastery experiences, increase confidence, and promote physical activity maintenance.

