### Limitations

This study protocol is not without limitations. First, given that only employees already enrolled in Change4Life (less than 10% of the eligible employee population) will be assessed for eligibility and invited to participate in the study, the results may not be generalizable. By recruiting only lower active Change4Life enrollees, we will learn more about how a higher risk employee population responds to incentives. Since the hallmark of Web-based health interventions is low engagement [49], there is potential for significant study dropout as well (ceasing daily device synchronization and not participating in assessments), especially among standard care participants. Both intervention and standard care participants will be encouraged to participate in all scheduled assessments (baseline, intervention end point, follow-up) with Can $10 (US $7.40) vouchers. Given the low participant burden and potential for lower active individuals to experience improved health, however, this voluntary incentive-based wellness program may be met with relatively high levels of engagement. Finally, participants will not be blinded to study group allocation, which could contaminate the results. Knowledge of group allocation will be assessed using a study exit survey to monitor this potential confounder.

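### Carrying week-12 means, measured while the incentive was paid, into missing week-24 data is not conservative for the primary comparison; the direction of bias depends on when participants drop out

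*Protocol article*

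**What the plan says.** The primary endpoint is fixed in Outcome Measures: "The primary study outcome will be the mean proportion of participant-days that step goals are achieved during week 24" (T3). The same section makes week 12 a secondary time point: "Mean proportion of participant-days that step goals are achieved during week 12 (intervention end point, T2".

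The Intervention Group section shows what differs between these two time points. "During the intervention period (weeks 3 to 12), intervention group participants will be eligible to earn Can $1" for each daily goal met; in weeks 13 to 24, "intervention participants will no longer receive the per day reward for reaching daily step goals". T2 therefore falls in the last paid week, and T3 comes 12 weeks after payment stops.

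For participants with too few synchronized workdays at T2 or T3, Statistical Analyses states that "the last observation will be carried forward using T1 or T2 means", and defends this with "This procedure conservatively assumes no change in variables and allows analysis by intention-to-treat". Step counts are dichotomized against the goal after this step.

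Two other statements bear on the rule. Of the five recent trials reviewed in the Introduction, "4 have observed a regression to baseline behaviors after incentive removal". The Limitations section says "there is potential for significant study dropout as well (ceasing daily device synchronization and not participating in assessments), especially among standard care participants".

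**The concern.** Assuming no change is cautious when the hypothesis is that something changes. Here the hypothesis is that a change produced under payment persists once payment ends. For someone seen at T2 but not at T3, no change from T2 means that the paid-period level lasted to week 24. The rule thus supplies the hoped-for answer for exactly the participants on whom there is no evidence, and only one arm loses an incentive between the two time points. Four of the five trials that the article cites point to the opposite course.

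At stake is the primary estimate. Imputed maintenance could be read as observed maintenance, under a label that tells readers any error runs the other way.

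**Working it through.** **The plan's own figure.** Sample Size gives 79 per group for 0.40 versus 0.20, 80% power, two-sided 0.05. With the unpooled two-proportion formula:

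(0.40×0.60 + 0.20×0.80) × (1.96 + 0.8416)² / 0.20² = 78.5, so 79 per group and 158 in all.

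This reproduces. The enrolment target of 174 (158 × 1.10, rounded) is 87 per arm.

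**Bias formula.** For each arm (I = intervention, C = standard care), let T2 and T3 be the true rates of meeting the goal, m2 the share missing T3 only (T2 carried), and m1 the share missing both T2 and T3 (T1 carried). Because means are carried and then dichotomized, a T1 mean scores 0: it is the baseline average, and the last goal in Table 1 is 3000 steps above it (assumed still to apply at week 24). A carried T2 mean scores 0 or 1 per person, so T2 below is the share of carried participants whose week-12 mean meets the goal. Taking dropout as unrelated to the outcome within arm:

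bias = m2_I(T2_I − T3_I) − m2_C(T2_C − T3_C) + m1_C·T3_C − m1_I·T3_I

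**Assumptions, not in the documents.** No true week-24 difference, T3 = 0.20 in both arms (the plan's standard-care rate); T2_I from 0.40 to 0.60; T2_C from 0.20 to 0.30; missing shares as shown.

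**T2 carried, equal shares in both arms**

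| Share carried | Smallest bias (T2_I 0.40, T2_C 0.30) | Largest bias (T2_I 0.60, T2_C 0.20) | Two-sided rejection at nominal 5% |
|---|---|---|---|
| 10% | 0.1×0.20 − 0.1×0.10 = +0.01 | 0.1×0.40 − 0 = +0.04 | 5.3% to 9.8% |
| 20% | +0.02 | +0.08 | 6.1% to 23.7% |
| 30% | +0.03 | +0.12 | 7.5% to 44.5% |

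Rejection rates use 87 per arm and the same binary variance as the sample size. Example: 0.24 versus 0.20 has SE √[(0.24×0.76 + 0.20×0.80)/87] = 0.063, so bias/SE = 0.64 and rejection is 9.8%. If averaging over days makes the true SE smaller, the rates rise.

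**T2 carried, more missing in standard care (10% versus 30%)**
- Standard care flat from T2 to T3: +0.02 to +0.04, the same as with equal 10% dropout.
- Standard care falling from 0.30 to 0.20: 0.02 − 0.03 = −0.01 up to 0.04 − 0.03 = +0.01.

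**T1 carried**
- 10% versus 30%, no true difference: 0.30×0.20 − 0.10×0.20 = +0.04 (rejection 11.1%).
- 10% in each arm, no true difference: 0.
- 10% in each arm, design rates: 0.9×0.40 − 0.9×0.20 = 0.18, so a true 0.20 is attenuated.

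The T1 figures depend on dichotomizing after carrying. If proportions of days were carried instead, and the daily SD were 3000 steps (assumed), about 16% of baseline days would reach baseline + 3000. The +0.04 would then become (0.30 − 0.10) × (0.20 − 0.16) = +0.008.

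**The case against.** The strongest defence is that the rule touches few people and does not always help the intervention. The planning dropout is 10%, where the T2 route adds at most 0.04 under these assumptions. Anyone lost before T2 is scored as failing, which is harsh on the intervention arm. Both arms receive retention vouchers at T2 and T3 regardless of goal attainment, and missing entries are to be compared between arms. All of this stands. It limits the size of the bias, but does not make the stated justification correct for participants who miss only T3.

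Three stronger readings are tempting, and the documents do not support them.

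- *The false difference is 0.06 to 0.12 at 10%/20% to 20%/40% dropout.* With T2_I = 0.40 and standard care flat, this requires every intervention loss to fall after T2 and every standard-care loss before it: 0.9×0.20 + 0.1×0.40 = 0.22 versus 0.8×0.20 = 0.16. At the same 10%/20%, all losses after T2 give +0.02, all before T2 give 0.18 − 0.16 = +0.02, and the reversed split gives 0.18 − 0.20 = −0.02. The article says nothing about the timing of dropout.
- *Higher standard-care dropout necessarily favours the intervention further.* It does so only where T1 means are carried. Limitations also speaks only of a potential for such dropout, and goes on to say that engagement may be relatively high.
- *Confidence intervals are too narrow because imputed values count as observed.* The plan bootstraps participants. Carry-forward is a fixed function of each participant's own data, so resampling captures the sampling variation of that estimator. The problem shown here is bias.

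The full analysis plan, which is not shown, may hold sensitivity analyses. Their absence from the article is not the point; the stated rule and its stated justification are.

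**Conclusion.** The point holds for the justification and for carrying T2 into week 24. The bias favours the intervention whenever its decline after T2, times its share missing only T3, exceeds the same product in standard care. That is the natural expectation if activity regresses when payment stops. The bias is modest at the planned dropout and reaches a sizeable part of the planned 0.20 only if about 30% of each arm has T2 carried. The T1 route can add to it or offset it. Week-12 rates, arm-specific dropout and its timing are all assumed, so no single net figure or sign can be claimed. A rule whose direction depends on unknown dropout timing, and which imputes the tested outcome for late dropouts, cannot be described as conservative.

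**What to change.** 1. Delete *conservatively*, and remove carry-forward from the primary analysis.
2. Fit the planned random-intercept logistic model to all observed valid participant-days at T2 and T3, keeping the planned covariates and participant bootstrap. Add a group-by-time term. The model as listed has time and treatment effects only, so without that term one treatment effect would blend the paid week 12 with week 24. This analysis rests on data being missing at random given T2, baseline covariates and arm.
3. Add two sensitivity analyses:
   - Count missing week-24 days as goal not met in both arms, stating that this favours the arm with less dropout. With 0.20 in both arms it gives 0.18 − 0.16 = +0.02 at 10%/20% and 0.16 − 0.12 = +0.04 at 20%/40%.
   - Use a multiple imputation that returns intervention dropouts to the standard-care distribution.
4. Report missingness by arm and by timing (before or after T2).

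The cost is wording and a little more analysis, with no change to design or data collection. The estimate may be less favourable or less precise.

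### Carrying a mean step count forward and then scoring it against the daily goal does not mean no change in the primary outcome, and is not reliably conservative

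*Protocol article*

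**What the plan says.** Under Outcome Measures: "The primary study outcome will be the mean proportion of participant-days that step goals are achieved during week 24".

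Under Statistical Analyses, a participant with fewer than three synchronized workdays at T2 or T3 is handled thus: "the last observation will be carried forward using T1 or T2 means". The justification follows: "This procedure conservatively assumes no change in variables and allows analysis by intention-to-treat". The next step is "The step count data will then be dichotomized at the participant-day level to create a binary variable", and the week-24 proportions are compared on that variable.

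The goal is set under Standard Care Group: "Change4Life will automatically calculate the average baseline value in the early hours of day 1, week 3 using data uploaded the previous 2 weeks". Table 1 there adds 1000, then 2000, then 3000 steps to that average. The entry for weeks 9-12 is "Maintain steps at 3000 above baseline average". Table 1 stops at week 12 and sets no goal for the run-in. For weeks 13-24 the protocol says only that "intervention participants will no longer receive the per day reward for reaching daily step goals"; it gives no goal value.

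**The concern.** The rule is justified as leaving variables unchanged. That is true of mean steps per day, a secondary outcome. It is not true of the primary outcome, which counts days at or above a threshold. Because the threshold is built from the T1 mean, comparing the T1 mean with it can give only one answer. A single T2 mean compared with a single threshold is all-or-none. At stake are the week-24 scores of everyone who fails the synchronization rule, and the claim that the imputation leans against the intervention.

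**Working it through.** **Planning values.** Sample Size assumes 0.40 vs 0.20 at week 24. With unpooled variance, (1.960 + 0.8416)² × (0.4×0.6 + 0.2×0.8) / 0.20² = 78.5, so 79 per group and 158 in total. The stated figure reproduces and is not in dispute. The two proportions are used below.

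**T1-carried days.** Let B be the run-in average. The goal and the analysis use the same screen (days under 100 or over 50,000 steps excluded), so the carried value is B. The goal is B + 3000 through week 12, assumed here to persist to week 24. B is below B + 3000, so every such day scores 0. Any goal above B gives the same result.

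If week-24 days really resembled run-in days, the share at or above B + 3000 would be 1 − Φ(3000/SD), with an assumed within-person day SD:

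| Day SD | Share of days at goal | Score under the rule |
|---|---|---|
| 2,000 | 0.067 | 0 |
| 2,500 | 0.115 | 0 |
| 3,000 | 0.159 | 0 |

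**T2-carried days.** Two illustrative weeks with a goal of 8000:
- 7000, 7200, 7400, 7600, 14000, 8200, 8100: mean 8500; observed proportion 3/7 = 0.43; carried score 1.
- 7000, 7200, 7400, 7600, 7700, 9000, 8500: mean 7771; observed proportion 2/7 = 0.29; carried score 0.

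For the average effect, assume normal steps, person SD 2,500, day SD 2,500 and a seven-day mean. Daily attainment is Φ(m/√(2500² + 2500²)) = Φ(m/3535.5). Attainment of the mean is Φ(m/√(2500² + 2500²/7)) = Φ(m/2672.6). The normal deviate is therefore multiplied by 3535.5/2672.6 = 1.323.
- 0.40: −0.2533 × 1.323 = −0.335, giving 0.369.
- 0.20: −0.8416 × 1.323 = −1.113, giving 0.133.

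The difference goes from 0.200 to 0.236, about 18% larger, among T2-carried participants only. If 10% are carried this way (the protocol's dropout rate), the trial-level shift is 0.10 × 0.036 ≈ 0.004. At 30% it is 0.011.

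A simulation with day SD 2,000-3,000 and person SD 1,500-2,500 (all assumed) gave 0.33-0.38 for 0.40 and 0.07-0.15 for 0.20. Across attainments of 0.20-0.60, between 47% and 92% of carried participants changed their proportion.

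**Direction with T1-carry**, scoring carried participants 0:
- Equal 10% carry: 0.40×0.9 − 0.20×0.9 = 0.18, so the planned 0.20 is diluted.
- 10% intervention, 30% standard care: 0.40×0.9 − 0.20×0.7 = 0.22.
- No true effect, 0.20 in both arms, 10% vs 20%: 0.18 − 0.16 = +0.02 for the incentive.
- No true effect, 0.40 in both arms, 10% vs 30%: 0.36 − 0.28 = +0.08.

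Part of this comes from carrying T1 at all. The part due to scoring the mean instead of the days is 0.10 × 0.067 to 0.10 × 0.159, that is 0.007-0.016 per 10-point imbalance in T1-carry. It is zero when carry is equal.

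**The case against.** Four points deserve weight.

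- **Replace or fill.** The trigger is fewer than three synchronized workdays, so a participant may still have some observed days. The text does not say whether the mean replaces them or only fills the gaps. A reader might infer that every carried participant becomes a certain failure or an all-or-none score. That follows only if the mean replaces all days. The statement about imputed days holds on either reading.
- **Another meaning of means.** The word could cover each variable's own mean, including the proportion. The stated sequence, with dichotomization after carry-forward, points against this. With no goal in weeks 1-2, a T1 proportion is also undefined unless a goal is supplied.
- **Direction.** A reader might infer that the rule systematically favours the incentive. The documents do not support that. Limitations raises greater dropout in standard care as a possibility, but also mentions retention vouchers in both arms and possibly high engagement. With equal T1-carry the effect is diluted.
- **Detail left to the full plan.** An article may omit imputation detail. Here, though, the rule, its order and its justification are all stated, and the result contradicts the justification.

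**Conclusion.** The point stands in limited form. As written, days imputed with the T1 mean always score 0, and days imputed with a T2 mean all score alike. This contradicts the stated no-change rationale for the primary outcome. It requires only the stated order of steps and a goal above the run-in average.

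The sizes rest on assumed SDs, on normality, on the goal staying at baseline plus 3000 to week 24, and on T2 attainment resembling the week-24 planning values. Under these the effect is small at trial level: about 0.004 from T2-carry if 10% are carried, and 0.007-0.016 per 10-point imbalance in T1-carry, against a planned 0.20. The 18% widening must not be read as a bias in the trial estimate, because it applies only to T2-carried participants. Calling the rule conservative is unsupported, since its direction depends on how carry-forward is distributed between arms.

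**What to change.** Dichotomize each observed day against the goal first, and never dichotomize a mean. Wherever carry-forward is used for the binary outcome, carry the participant's observed proportion of days at or above the week-24 goal, with T1 days scored against that same goal. State that goal, and say whether carried values replace or supplement any observed days. Delete the word *conservatively* from the justification.

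The cost is minor reprogramming on daily data already collected, with no extra participants. This does not remove the dilution or imbalance that comes from carrying T1 forward at all. Whether the primary analysis should use another missing-data method is a separate decision with its own costs.
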